#### Subgroup analysis

2.10.5

The analysis will also be stratified by age, and each year group (eg, 75 yr, 76 yr, etc.) will be presented separately. A comparison between the pooled trials and the age stratifications will be described, and whether a potential benefit/no benefit is observed in certain age groups will be reported. Additionally, a subgroup analysis would be performed among men with Charlson Comorbidity Index ≤10, as the group with Charlson Comorbidity Index >10 might rarely be offered PSA-based screening.

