#### Survival analysis

2.10.4

The analysis will be conducted using Stata 18 (Stata Corporation, College Station, TX, USA). Flexible parametric survival models will be used to model the log cumulative hazard with natural splines. Selection of the number of degrees of freedom for the baseline hazard will be done by evaluating the Akaike's Information Criteria [23]. Time-dependent coefficients will be used to account for a potential time-varying effect of the screening. Since men can participate in several trials, the variance-covariance matrix will be estimated using the clustered sandwich estimator. The stabilized inverse probability of screening weighting (IPW) will be generated using logistic regression. In presence of extreme weights, IPW will be truncated at the 99th percentile [21] and then multiplied by the IPCW. The product will be used to weigh the likelihood of the flexible parametric models. The user-written command stpm3 will be used to fit the flexible parametric survival models [24].

Standardized model-based cumulative incidence functions (CIFs) will be plotted and reported for all outcomes, and the difference in CIFs will also be plotted and reported at 5, 10, and 15 yr of follow-up. Standardization will be done over the empirical distribution of the confounders using the command standsurv [25]. The CIF difference for both the PCa-specific mortality and the all-cause mortality will be reported.

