### Power calculation

2.12

The STHLM0 and STHLM0+ combined have >200 000 men in the eligible age group between 2007 and 2023 [22]. Considering life expectancy of 11.5 yr on average for men aged 75–79 yr and 10 yr for men aged 80 yr, we can assume that, with a minimum of 200 000 men eligible for the study and 12 500 men enrolled each year, around 35 000 deaths would be recorded during the follow-up from 2007 to 2023. Hence, assuming a baseline cumulative mortality of 0.80 after 17 yr and a proportion of screening of 20%, Table 1 summarizes the power according to five different scenarios of potential reduction in mortality. Based on the power calculations, the study is powered sufficiently (>90%) to detect a benefit of at least 1.5% absolute mortality reduction. A minimum of 1.28% absolute risk reduction is necessary to guarantee at least 80% power.

**Table 1 t0005:** Power calculations for all-cause mortality

ARR (%)	HR^a^	Power with 35 000 deaths (%)	Minimum deaths needed for 80% power
1.0	0.970	62.5	∼52 700
1.5	0.956	92.0	∼24 200
2.0	0.941	99.6	∼12 800
2.5	0.927	>99.9	∼8500
3.0	0.913	>99.9	∼5930

ARR = absolute risk reduction; HR = hazard ratio.

a Hazard ratios are approximates based on the baseline mortality and the absolute reductions.

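### Section 2.10.5 reads the effect of age from separate single-year findings of benefit or no benefit, which gives no valid comparison between ages

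*Protocol article*

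**What the plan says.** The protocol article, Section 2.10.5 (Subgroup analysis), sets out how the effect of age will be read. "The analysis will also be stratified by age, and each year group (eg, 75 yr, 76 yr, etc.) will be presented separately". Next to these strata the pooled result is set: "A comparison between the pooled trials and the age stratifications will be described". The section adds, as what the reader is to be told, that "whether a potential benefit/no benefit is observed in certain age groups will be reported". No contrast between ages is part of this description, and benefit is not defined.

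Sections 2.5 and 2.10.2 start a new emulated trial at every month of age across the range, so one man can contribute at 75, 76 and later. Section 2.10.4 deals with this for the pooled model: "Since men can participate in several trials, the variance-covariance matrix will be estimated using the clustered sandwich estimator".

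Section 2.12 gives power for the pooled all-cause analysis only. It expects that "around 35 000 deaths would be recorded during the follow-up from 2007 to 2023" and concludes that "the study is powered sufficiently (>90%) to detect a benefit of at least 1.5% absolute mortality reduction". It gives neither deaths nor power by year of age.

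**The concern.** There are three difficulties with the rule as written.

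- A finding of benefit at one age and none at another is not evidence that the effect differs between those ages. That needs an estimate of the difference with its own variance.
- The comparison offered instead sets each stratum against a pool that contains it, which pulls the two together by construction.
- The strata share men. Separate fits, each with its own clustered variance, leave the covariance between strata unknown, so the variance of an age difference cannot be recovered from them.

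The Discussion opens by asking when screening should be discontinued, and Section 3.1 foresees that guidelines may be informed by the result. A chance pattern by single year could be taken for an age at which benefit ends.

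**Working it through.** **Inputs.** From Section 2.12 and Table 1: 35 000 deaths, 20% screened, and a hazard ratio of 0.956 for a 1.5-point absolute reduction. From Section 2.10.5: five strata (75, 76, 77, 78, 79). Assumed, because the document does not state them: two-sided alpha of 0.05, the number of deaths per stratum, and the correlation between stratum estimates. No loss of information from weighting is allowed for.

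**The plan's own figure.** Power = Φ(√(D × 0.2 × 0.8) × |ln HR| − 1.96). With D = 35 000: √5600 = 74.83; 74.83 × 0.0450 = 3.367; Φ(1.407) = 92.0%. This matches Table 1, so the alpha assumption is consistent with the plan.

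**One stratum.** An equal split without overlap gives 35 000 / 5 = 7000 deaths. √1120 = 33.47; 33.47 × 0.0450 = 1.506; Φ(−0.454) = 32.5%. At 7000 deaths, power is 17% for a 1.0-point reduction, 53% for 2.0, 72% for 2.5 and 86% for 3.0. If overlap raises each stratum to 14 000 deaths, power at 1.5 points is 57%.

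**Mixed pattern, benefit read as significance.** The relevant event is that some but not all of the five strata are significant although the true effect is the same in each. For independent strata it is 1 − p⁵ − (1 − p)⁵. With p = 0.325: 1 − 0.004 − 0.140 = 85.6%. For correlated strata it was simulated from an equicorrelated normal model (400 000 draws), at 1.5 points:

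| Deaths per stratum | Power | Independent | ρ 0.3 | ρ 0.5 | ρ 0.7 | ρ 0.9 |
|---|---|---|---|---|---|---|
| 7000 | 32.5% | 86% | 71% | 60% | 46% | 27% |
| 14 000 | 57% | – | 78% | 66% | 51% | 29% |
| 35 000 | 92% | – | 28% | 24% | 19% | 11% |

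The last two rows need deaths shared between strata, so independence is not assumed there. The 35 000 row is an extreme bound, in which every planned death counts in every stratum. By construction, a valid joint test at 0.05 declares a false difference in 5% of cases.

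**Mixed pattern, benefit read as the sign of the estimate.** At 7000 deaths each estimate has the right sign with probability Φ(1.506) = 0.934. For independent strata, 1 − 0.934⁵ = 29%. At ρ = 0.5 the simulation gives 21%.

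**Stratum against pool.** If five non-overlapping strata carried equal weight, the stratum minus the pool would equal 4/5 of the stratum minus the mean of the other four. The comparison therefore understates the contrast of interest even in the simplest case.

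**Variance of an age difference.** Var(a − b) = Var(a) + Var(b) − 2 Cov(a, b). Separate fits give the first two terms only.

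**The case against.** The text is descriptive. It states no significance threshold, Section 2.10.4 reports CIF differences rather than verdicts, and power is claimed only for the pooled analysis. Nowhere does the article commit to choosing a stopping age from single-year strata, and the implications in Section 3.1 are framed for ages 75–79 as a whole. All of this stands. It limits the size of the problem, but a descriptive benefit/no benefit statement by year of age still invites the comparison that the method cannot support.

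A condensed article may leave a heterogeneity test to a fuller plan. That is fair, and the absence of a named test is not the point here. The point rests on the reading rule that the article does state.

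Two stronger readings are tempting and should be resisted.

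- A reader might infer that false differences are almost certain, since 1 − 0.325⁵ = 99.6%. That figure is the chance that at least one stratum misses significance. It includes the 14% of cases in which all five miss, which shows no difference between ages. It also rests on independent strata and an equal split, and that split sits badly with the overlap: a man followed from 75 may be counted again at later ages, so a stratum can hold more than a fifth of the deaths.
- A reader might infer that shared men cause the false differences. Positive correlation works the other way and makes the strata agree more often. Sharing matters because it leaves the variance of an age difference unknown.

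**Conclusion.** The concern holds for the reading rule in Section 2.10.5: it provides no valid contrast between ages, and separate fits cannot supply one when men recur across strata. Under a constant 1.5-point reduction, with 7000 deaths per stratum, two-sided 0.05 and benefit read as significance, a mixed pattern would arise in about 86% of cases if strata are independent and in roughly 27% to 71% over correlations of 0.9 to 0.3. Read from the sign of the estimate, it is about 21% to 29%.

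These sizes are conditional. The document gives no deaths by age, the correlation cannot be derived from it, and benefit is undefined. The one-third power is therefore a single assumed case and not a property of the plan. The flaw in method does not depend on any of these figures.

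**What to change.** In Section 2.10.5, judge the effect of age within the pooled weighted model of Section 2.10.4. Add a screening-by-age-at-time-zero interaction, including its terms with the time-dependent screening effect, keep the variance clustered on the man across all trials, and report the joint test of the interaction. Present standardized CIF differences with confidence intervals at each age from that model. Replace the per-stratum benefit/no benefit statement, and the comparison of a stratum with the pool containing it, by this contrast.

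The cost is one further and somewhat larger model on the dataset already planned. The single-year results can still be shown. The interaction test may have limited power, so the text should say that a null result will not be reported as proof of a constant effect across ages.

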#### Data preparation and choice of confounders

2.10.1

Data on all men living in Stockholm will be used, and ascertainment of time zero will be performed for all eligible men with no information on the variables necessary for the analysis missing. As men can continuously be eligible to be included in the sequential trials, the choice of time zero will follow the recommendation of Hernán et al [17], and emulation will be done repetitively during the eligibility period between 2007 and 2023. The confounders of interest are age (continuous), trial year (categorical; from 2007 to 2023), country/region of birth (categorical; Sweden, Nordic, European Union, and others), income (categorical; five quintiles), previous hospitalization during the past year (yes/no), number of hospitalizations during the past year (continuous), number of outpatient specialized health care visits (continuous), non–age-adjusted Charlson Comorbidity Index (continuous, based on adaptations for register-based Swedish data [20], and cumulatively computed, based on the past 5 yr until the end of the previous calendar year before the assessment), education (categorical; ≤9 yr of formal education, 10–12 yr of formal education, and ≥12 yr of formal education), civil status (categorical; not married, married, divorced, and widowed), current cancer diagnosis excluding PCa (yes/no), and family history of PCa (yes/no, based on father, brother[s], or son[s] diagnosed with PCa).

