### Potential strengths and limitations

3.3

Our study will leverage the STHLM0, which has near complete information on all PSA tests in Stockholm, with linkage to national Swedish registers allowing the capture of diverse lists of potential confounders [22]. In our planned study, we consider the emulation of pragmatic target trials suitable for addressing the research questions at hand. Moreover, the potential follow-up of up to 17 yr can provide sufficient time for the relevant outcomes to occur. Henceforth, this work has the potential to guide decisions on PCa screening cessation, addressing an important need among men who undergo opportunistic testing despite the lack of guidelines for this age group.

Despite these considerations, the study has potential limitations. First, our analysis plan assumes adherence to the assigned arm at each trial, which might not be ideal. Some of the men who will be considered as screened might have been prompted to undergo a PSA test following the symptoms of metastasis or urinary retention. However, the cause of the PSA test cannot be discerned from the register data. The diagnosis if preceded by symptoms is captured in the register but has incomplete information [39]. Additionally, men who underwent a PSA test within the study period due to health checkup following previously elevated tests are classified as screened in the study. However, due to the shift to organized PCa testing [40], this approach might better reflect future screening directions of continuing screening in this age group that was initiated at an earlier age, instead of initiating screening in this age group. Second, unmeasured and residual confounding cannot be ruled out, and data on functionality, holistic objective health status, and disability are not available from the registers. Although we attempt to conduct a subgroup analysis based on the level of multimorbidity excluding those who are sickest, it would not granularly capture individual causes of the PSA testing. Additionally, men who are institutionalized might not have admission or usage of specialized outpatient care, underestimating their multimorbidity.

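### The Charlson ≤10 subgroup very probably keeps almost the whole cohort, and the index can be almost 12 months out of date at time zero

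*Protocol article*

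**What the plan says.** Section 2.10.5 (Subgroup analysis) of the protocol article plans that a "subgroup analysis would be performed among men with Charlson Comorbidity Index ≤10", and gives the reason "as the group with Charlson Comorbidity Index >10 might rarely be offered PSA-based screening". Section 3.3 (Potential strengths and limitations) describes the same analysis as "a subgroup analysis based on the level of multimorbidity excluding those who are sickest", and concedes that it will not show in detail why individual men were tested.

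Section 2.10.1 (Data preparation and choice of confounders) defines the measure as a "non–age-adjusted Charlson Comorbidity Index (continuous, based on adaptations for register-based Swedish data", computed cumulatively and "based on the past 5 yr until the end of the previous calendar year before the assessment". The same list holds "previous hospitalization during the past year (yes/no), number of hospitalizations during the past year (continuous"), the number of specialized outpatient visits (no time window stated) and a yes/no item for current cancer other than prostate cancer.

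Sections 2.5 and 2.10.2 start a new emulated trial every month. Section 2.10.2 uses the confounder list for the censoring weights. Section 2.10.4 adds screening weights and standardization over the confounders.

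**The concern.** There are two separate weaknesses, both in rules that the plan states.

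**The cut-point.** This is the only planned analysis that restricts the cohort by health status. If hardly any man scores above 10, the restricted analysis is the main analysis over again. Agreement between the two would look like reassurance about frail men but would carry almost no information. Section 3.3 adds that institutionalized men may have their multimorbidity underestimated, so some frail men would score low and stay in whatever the cut.

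**The timing of the index.** Exchangeability (section 2.5) depends on confounders that describe the man at time zero. A condition first recorded in January does not reach the index until the following January, although up to twelve monthly trials start in between. Hospitalization is counted over the past year, so the health covariates do not share one time window. Section 3.3 says that function, overall health status and disability are not in the registers. That is a reason to use the available health data as fully as possible.

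**Working it through.** **No figure to reproduce.** The document does not give the share of men with an index above 10, or any distribution of the index. The shares below are therefore assumptions shown as a range. They do not use the Charlson item weights, which the document does not list.

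**Step 1: share above 10.** Let the index have mean m and variance/mean ratio v. For v = 1 use a Poisson distribution. For v > 1 use a negative binomial with p = 1/v and size r = m/(v − 1). Percentage of men with an index above 10:

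| Mean | v = 1 | v = 2 | v = 3 | v = 4 |
|---|---|---|---|---|
| 1 | 0.000 | 0.049 | 0.314 | 0.696 |
| 1.5 | 0.000 | 0.139 | 0.652 | 1.285 |
| 2 | 0.001 | 0.317 | 1.156 | 2.059 |
| 2.5 | 0.006 | 0.629 | 1.857 | 3.035 |
| 3 | 0.029 | 1.123 | 2.783 | 4.224 |

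Three cells can be checked by hand, because r = 1 makes the distribution geometric and P(index > 10) = (1 − 1/v)^11:
- m = 1, v = 2: 0.5^11 = 0.049%
- m = 2, v = 3: (2/3)^11 = 1.156%
- m = 3, v = 4: 0.75^11 = 4.224%

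**Step 2: men kept.** Section 2.12 gives more than 200 000 men. At the largest share, 200 000 × (1 − 0.04224) ≈ 191 550 stay in, about 96%. At the smallest share, nearly all do.

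**Step 3: how far the result can move.** For a risk difference standardized over the cohort, with share s excluded,

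D(all) = (1 − s) × D(kept) + s × D(excluded), so D(all) − D(kept) = s × [D(excluded) − D(kept)].

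The smallest reduction in Table 1 is 1.0 percentage point. For the subgroup result to differ from the main result by that much, the arm difference in excluded men must differ from that in the others by 1.0/s:
- s = 4.224%: 1.0/0.04224 ≈ 24 percentage points
- s = 2.059%: 1.0/0.02059 ≈ 49 percentage points
- s = 1.156%: 1.0/0.01156 ≈ 87 percentage points

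This treats s as the share of person-trials and leaves aside any extra influence of large weights, which section 2.10.4 would truncate at the 99th percentile.

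**Step 4: age of the index.** On the first of each month the gap since 31 December is 0, 1, …, 11 months, with mean 66/12 = 5.5. That fits the calendar-year sensitivity analysis. In the main analysis time zero is the date an age is attained, which can fall on any day of the month. The gap then runs from 0 to just under 12 months, and averages about 6 if those dates are spread evenly.

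**The case against.** The strongest reply to the first part is that section 2.10.5 gives a positivity reason: drop the men who are hardly ever offered a test. A positivity trim normally removes a small tail, so keeping most men is not in itself a failure. That stands for the trim. It does not rescue the description in section 3.3, where the same analysis is said to leave out the sickest men. Section 3.3 admits that the subgroup is coarse, but not that it may remove almost nobody.

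On the lag, the index is refreshed each January, and ending it before time zero keeps out post-baseline information. A new serious illness will often also show as an admission, a specialist visit or a current cancer, all of which are on the confounder list. This stands in large part. What is lost is the diagnosis-specific part of the information for some months. Avoiding post-baseline information does not require the lag, since a look-back ending the day before time zero avoids it too.

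A reader might infer that comorbidity control as a whole does little. The documents do not support that: adjustment rests on the continuous index and the other health variables, through both sets of weights and standardization, and the ≤10 cut touches none of it. The subgroup is also not the main safeguard against confounding, since section 2.11.2 plans an array analysis for unmeasured confounders.

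A reader might also infer a bias in favour of screening as large as the effect sought. Nothing in the document links the lag or the cut to a particular hazard ratio. The direction is open too: sections 2.10.5 and 3.3 suggest that very sick men are tested less, while sections 2.6 and 3.3 describe symptoms that prompt a test.

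**Conclusion.** Both rules are weaker than they need to be. The ≤10 subgroup very probably cannot serve as an analysis without the sickest men. The 96% to nearly 100% retained rests on the assumed means and variance/mean ratios, so *very probably* is as far as the claim goes until the index distribution is reported. The lag follows directly from the stated definition and needs no distributional assumption, but its effect on the estimates is unknown.

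The point is minor to moderate. It concerns a secondary analysis and the timing of one covariate among several, and part of the limitation is already acknowledged. It is worth acting on because the changes are cheap.

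**What to change.** 1. For each monthly trial, compute the index on the 5 years ending the day before time zero, in both the age-based and the calendar-year analysis.
2. Report the distribution of the index, with the number of men and of person-trials at each level.
3. Before outcome data are examined, replace or supplement the ≤10 cut with a lower cut-point or with strata that actually divide the cohort, for example 0, 1–2 and ≥3. If the ≤10 cut stays, describe it as a positivity trim and reword section 3.3 accordingly.

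The cost is in definitions and code: a rolling covariate has to be computed for every trial, and smaller subgroups will have wider intervals. No new data source is needed if the linked registers hold dated diagnoses.

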### Sensitivity analysis

2.11

#### Analysis based on calendar year

2.11.1

Emulated target trials with observational analog of an intention-to-screen analysis will be conducted, using the CCW method and sequential design every month in alignment to the main analysis. However, the month’s assessment will start from January 1, 2007. Men are ascertained for their screening within the month if they are eligible (75–79 yr). The intervention arm includes eligible men screened with PSA for PCa, while the control arm includes eligible men not screened for PCa during that specific month period. Follow-up starts on January 1, 2007 and ends on December 31, 2023, or when mortality occurs, whichever comes first.

Figure 1B illustrates the flowchart of the inclusion into the trial based on the sensitivity analysis.

#### Other sensitivity analysis considerations

2.11.2

In addition to the different causal inference methods, this study will consider limiting the recruitment period to December 2018 and December 2013 to allow for longer follow-up time among eligible men. We will consider extending the ascertainment period of the PSA-based screening to 12 mo instead of 6 mo. A deterministic sensitivity analysis for unmeasured confounding using the array method, as described by Schneeweiss [26], will be performed, and the curved surface representing the “fully” adjusted ratio based on the assumed prevalence and varied strength of the unmeasured confounder will be plotted. Moreover, the results will be contrasted with men aged 65–69 and 58–62 yr (in contrast to men aged 75–79 yr).

